### Recruitment and participants

Eligible patients will be recruited from the outpatient department or clinical wards consecutively with written consent in the listed hospitals. Their medical history will be kept in the medical record system. Before signing the surgery consent form, all participants will have the objectives, benefits, and risks of the operation as well as their rights and responsibilities explained to them. Patients who are assessed as eligible will be randomly allocated to the RN (robotic natural orifice specimen extraction surgery) and RA (traditional robotic-assisted surgery) group. The allocated participants in each group will undergo corresponding modus operandi detailed in the “Intervention” section. All participants or their legal representatives will sign the consent for operation. On the consent form, participants will be asked if they agree to have their data used should they choose to withdraw from the trial. Participants will also be asked for permission in order to share relevant data with collaborators taking part in the research or from regulatory authorities, where relevant. The enrollment and randomization flow chart is shown in Fig. 1.

**Fig. 1 Fig1:**
[figure not shown]
Consolidated Standards of Reporting Trials (CONSORT) flow diagram

### Sample size

A previously published study observed that the complication rate of robotic-assisted colorectal surgery is 17% [12]. According to the retrospective analysis in the medical record system at our institution, the complication rate of traditional robotic-assisted surgery is around 15%. As for the non-inferiority margin, no published studies can be referenced to our knowledge. After a close discussion with the investigators involved in this trial, the margin was set to 10%. We assume that this trial has 80% power (1-β) to detect the complication rate difference between the experimental and control group and a one-sided significance level of 0.025(α = 0.025). Accordingly, 402 participants in total are needed (201 per group). Considering that the overall dropout rate is 20%, we calculated that 503 participants should be enrolled in the study. Finally, 550 participants were recruited in this trial. The sample size was calculated using PASS 11 (version 11.0.7).

### Randomization and blinding

Stratified block randomization was performed by the Division of Data Management with a block size of 4. The assignment list was generated by a computer program in a block of four and was stratified by cT stage and hospital, which will be sent to the corresponding collaborators of each hospital via e-mail. Participants will then be randomly assigned to an experimental and control group with a 1:1 ratio according to the assignment list. The Division of Data Management will be blinded to the medical data except cT stage and hospital to avoid nonrandom allocation. The patients and the surgeons will not be blind to the allocation.

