### Trial design

This study is a prospective, open-label, randomized controlled, parallel-group, multicenter, and non-inferiority trial conducted in seven academic hospitals in China. The hospitals involved are shown in Table 1.

**Table 1 Tab1:** Collaborator hospitals, locations, principle investigator/collaborator and anticipated participants

Hospitals	Locations	Names	Role in this study	Anticipated participants
The First Affiliated Hospital of Nanchang University	China, Jiangxi	[name],	Principle investigator	130
		[name]	Steering committee	
		Division of data management	Data management team	
The Second Xiangya Hospital of Central South University	China, Hunan	[name]	Collaborator	70
Nanfang Hospital, Southern Medical University	China, Guangdong	[name]	Collaborator	70
First Affiliated Hospital of Gannan Medical College	China, Jiangxi	[name]	Collaborator	70
Zhongshan Hospital, Fudan University	China, Shanghai	[name]	Collaborator	70
Chinese PLA General Hospital (301 Hospital) China	China, Beijing	[name]	Collaborator	70
The Second Affiliated Hospital of Nanchang University	China, Jiangxi	[name]	Collaborator	70

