### Exclusion criteria

The exclusion criteria are as follows:
Not suitable for robot laparoscopic surgery;The tumor is too large to be pulled out through the anus or vagina;Simultaneous multiple primary cancers;Emergency surgery due to complication (bleeding, obstruction, or perforation) caused by primary cancer; andWomen with acute gynecological infections, vaginal deformities, unmarried and infertile women, and women who are married and plan to get pregnant.

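### The stratified assignment list, in fixed blocks of four, is e-mailed to the hospitals of an open-label trial before patients are assigned, so allocation is not concealed from the sites that recruit

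*Protocol article*

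**What the plan says.** The section Randomization and blinding of the protocol article describes the mechanism in five steps.

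- **Generation:** "Stratified block randomization was performed by the Division of Data Management with a block size of 4".
- **Distribution:** the list is "stratified by cT stage and hospital, which will be sent to the corresponding collaborators of each hospital via e-mail".
- **Use:** "Participants will then be randomly assigned to an experimental and control group with a 1:1 ratio according to the assignment list".
- **Safeguard:** "The Division of Data Management will be blinded to the medical data except cT stage and hospital to avoid nonrandom allocation".
- **Blinding:** "The patients and the surgeons will not be blind to the allocation".

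Under Recruitment and participants, "Eligible patients will be recruited from the outpatient department or clinical wards consecutively with written consent in the listed hospitals". Table 1 lists the seven hospitals, six with a collaborator and one with the principal investigator. The exclusion criteria include a judgement about extraction: "The tumor is too large to be pulled out through the anus or vagina". They also exclude patients unsuitable for robotic surgery. The article describes no central release, sealed envelopes or other concealment step.

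**The concern.** Randomization protects the comparison only if those who decide whether a patient enters cannot know the next arm. Here the list leaves the Division and goes to the hospitals that recruit. The safeguard covers the Division, which does not choose patients, and leaves the sites uncovered.

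This is more than detail left to a fuller document. The article says how allocation is handled, and that method discloses the sequence.

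Someone who knows the next arm has room to act on it. Whether a tumor is too large to extract, or a patient is unsuitable for robotic surgery, is partly a matter of judgement. With separate sequences by cT stage, a borderline staging call could also decide which sequence applies. The primary outcome, complications within 30 days, plausibly depends on case difficulty, so a difference in case mix between the arms would feed directly into the non-inferiority comparison.

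Fixed blocks of 4 are a second, smaller weakness. In an open-label trial with a published block size, earlier allocations reveal later ones even when the list is withheld.

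**Working it through.** **1. What the holder of the list knows.** No arithmetic is needed. The list is sent, patients are then assigned from it, and nothing in the text hides later entries from the recipient. For a person holding a hospital's list, 100% of upcoming allocations at that hospital are known. Table 1 gives 130 + 6 × 70 = 550 anticipated participants, which matches the stated total, so the mechanism covers the whole trial.

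**2. What can be predicted without the list.** Inputs from the article: block size 4, ratio 1:1, open label. Assumptions: blocks are completed, and the guesser tracks all earlier allocations in the same hospital and cT stratum. The number of cT levels is not stated, but the shares do not depend on it.

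There are 6 equally likely orders of AABB, hence 6 × 4 = 24 positions.

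- *Certain positions.* AABB and BBAA each have 2, because after two of a kind the last two are fixed. ABAB, ABBA, BAAB and BABA each have 1. The total is 2 × 2 + 4 × 1 = 8, and 8/24 = 33.3%.
- *Correct guesses, always choosing the arm with more places left.* Position 1: 1/2. Position 2: 2/3. Position 3: 1/3 × 1 + 2/3 × 1/2 = 2/3. Position 4: 1. The mean is (0.500 + 0.667 + 0.667 + 1)/4 = 70.8%.

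| Situation | Certain | Guessed correctly |
|---|---|---|
| List in hand | 100% | 100% |
| List withheld, fixed blocks of 4 | 33.3% | 70.8% |
| List withheld, fixed blocks of 6 | 25.0% | 68.3% |
| Simple randomization | 0% | 50% |

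For 550 patients and blocks of 4, that is 550 × 0.333 ≈ 183 certain and 550 × 0.708 ≈ 390 guessed correctly. A larger fixed block helps only a little.

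**3. A hypothetical bias.** None of the following inputs is in the documents. Suppose one third of patients are high risk, with complication rates of 25% against 10% in the rest. The average is 1/3 × 25% + 2/3 × 10% = 15%, which agrees with the control rate under Sample size. Suppose also that a fraction f of the high-risk patients due for the natural-orifice arm (RN) is exchanged for low-risk patients due for the control arm (RA). Then

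shift in RN − RA = −2 × f × 1/3 × (0.25 − 0.10).

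- f = 0.1: −0.010, or −1 percentage point.
- f = 0.3: −0.030, or −3 percentage points.

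The margin is 10 points. Steering in the opposite direction reverses the sign. The exercise shows only that modest steering could matter; it does not estimate what will happen.

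**The case against.** **The recipients are not said to recruit.** A reader might infer that the surgeons who recruit and operate hold the list. The text does not say so. It names one collaborator or investigator role per hospital and gives that role no screening or operating duty. This stands, and it limits the claim: concealment is unprotected at the recruiting hospitals, but it is not shown that recruiters look up the next arm.

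**Another reading of the mechanism.** The Division is blinded to medical data except cT stage and hospital. A unit that only prepares a list in advance would not need any patient's cT stage, so the exception could hint at patient-by-patient handling. Eligibility is also assessed before allocation. But it is the list that is described as being sent, with assignment following from it. If the intention was different, the text needs correcting anyway.

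**Steering is constrained.** Recruitment is to be consecutive, the trial is stratified by hospital and cT stage, and eligibility is narrow (ECOG 0 or 1, T1-3N0M0, tumor more than 10 cm from the dentate line). These limit deferral and the available case mix. They do not conceal allocation, and they leave the judgement criteria in place.

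**Block size.** Fixed blocks of 4 are common, and the predicted shares assume a guesser who tracks every stratum. This stands, so the block size is the secondary part of the point.

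**Conclusion.** The concern holds as a defect in the stated mechanism. As written, the sequence is disclosed to the hospitals before patients are assigned in an open-label trial, and the only safeguard named does not address that. It should be corrected because it bears on the validity of the primary comparison. The conclusion rests on the plain reading that the list itself is sent ahead of assignment.

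Two stronger readings are not supported. A reader might infer a bias of 1 to 3 points in favour of RN, but that range comes entirely from assumed risks and swap rates. The documents settle neither the size nor the direction. A reader might also infer that no analysis could help. Adjustment for measured baseline factors could reduce such a bias, but it cannot be relied on to remove what was not measured.

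The 33.3% and 70.8% are exact for completed blocks of 4 and apply even if the list is withheld.

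**What to change.** - **Main change.** Keep the list at the Division of Data Management. Release one allocation per request, by e-mail reply, phone or web, only after consent, eligibility and cT stage have been logged and can no longer be changed.
- **If lists have already been sent.** Generate fresh ones for the remaining patients. The Trial status section already provides a route for amendments.
- **Secondary change.** Use randomly varying block sizes (for example 4, 6 and 8) and do not disclose them to the sites. Some guessing above 50% will remain, but a site that does not know where a block ends can seldom be certain of the next arm.
- **Text.** State who at each hospital requests and receives the allocation.

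The cost is low, since the Division already holds the list and uses e-mail. Each enrolment needs one contact, and within-stratum imbalance may be slightly larger. The figures of 402 evaluable, 503 after dropout and 550 enrolled are unaffected.

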### Intervention

Patients will be randomly allocated into the RA (traditional robotic-assisted surgery) group and RN (Robotic natural orifice specimen extraction surgery) group. The specimen will be extracted through the rectum and vagina [13, 14]. In terms of female participants, in principle, extracting the specimen through rectum will be prioritized. This is a surgical trial; there are no strategies for patients to improve adherence. All the surgeons included in this study perform more than 100 robotic gastrointestinal surgeries a year. In order to make surgeons adhere to intervention protocol, critical surgical nodes will be photographed. And these photos will be submitted to the Division of Data Management. The Research Committee will check the surgical quality. The non-adherent cases will be excluded from per-protocol analysis. The schedule of this trial is shown in Fig. 2.

**Fig. 2 Fig2:**
[figure not shown]
Schedule of assessment. CD3 cluster of differentiation 3, CD4 cluster of differentiation 4, CD8 cluster of differentiation 8

### Traditional robotic-assisted surgery

Patients will be performed traditional robotic-assisted colorectal resection following the total mesorectal excision(TME) principle. All patients are intubated under general anesthesia in the lithotomy position. We employ the 5-hole trocar layout. The navel is used to explore the abdominal cavity, and two operation holes are established on the right and left lower abdomen. The peritoneum is incised at the junction of the sigmoid mesocolon and the pelvis to find the inferior mesenteric vessels. Clamp and cut off the inferior mesenteric vessels while the left colonic vessels are kept as far as possible, with the surrounding lymph nodes being thoroughly cleaned. After entering the Toldts gap, the naked sigmoid colon and rectum are freely exposed outward and downward, and the rectum is cut off with a linear cutter stapler and cartridge approximately 3 to 5 cm under the lower edge of the tumor. The abdomen is then entered layer-by-layer and the incision protector is placed through a midline abdominal incision with a length of 5 to 6 cm. Afterward, the proximal intestine is removed, and a specimen is cut off from the colonic mesocolon 10 to 15 cm upper the tumor. After disinfecting the cut edge, the intestine is placed into the stapler holder and undergoes an external purse-string suture into the abdominal cavity. Pneumoperitoneum is then reestablished, and the stump of the intestine is flushed from the anus. Then, the stapler is placed, and the end-to-end anastomosis is completed under the endoscope. Finally, a rubber drainage tube is placed and fixed on the left abdominal wall next to the anastomosis from the trocar hole.

### Robotic natural orifice specimen extraction surgery via rectum

Patients will receive robotic colorectal resection with natural orifice specimen extraction surgeries through the rectum or vagina. After general anesthesia, the 5-hole method is used in the lithotomy position with the right thigh placed horizontally. After cutting the first incision in the mesorectum at about 3–5 cm below the sacral headland, the Toldts gap is then entered, freeing the root of the inferior mesenteric vessels and separating the bare inferior mesenteric vessels layer-by-layer with a pre-cut line, which is then ligated and cut. The mesorectum is freed, after which the avascular area of the sigmoid mesocolon is opened, while the rectal mesentery is freed downward and outward to the bifurcation of the left common iliac and separated downward along the anterior iliac gap. After the inferior hypogastric plexus is exposed, an ultrasonic knife is used to carry out separation at a uniform speed along the nerve surface. This process simultaneously frees the left and right sides of the rectum 3–5 cm below the tumor. After determining the location of the tumor, intestinal wall nakedness is performed within a range of about 3 cm within 5 cm below the tumor. The sigmoid colon is then exposed for about 2 cm, after which the sigmoid mesenteric vessels are ligated and cut and the pre-cut line is determined. The assistant then fully expands and washes the anus, and an iodine gauze ball is placed under the tumor to indicate the intestinal incision. After the intestinal incision is made, the assistant places the stapler holder from the anus into the abdominal cavity through the intestinal incision for backup. At the same time, a longitudinal incision is made on the intestinal wall above the tumor. The iodine gauze is sterilized and inserted into the intestine through the longitudinal incision. The intestinal canal is then cut and closed with a linear cutter stapler and cartridge above the longitudinal incision. The rectum is subsequently severed using an ultrasonic knife at the incision below the tumor. The assistant then places the specimen into the protector through the anus by the oval forceps outside and clamps the specimen out of the anus using the oval forceps. The cutter stapler and cartridge close the stump of the distal rectum canal, and the annular stapler is then inserted through the anus. The stapler holder is then docked with the body to complete the end-to-end anastomosis. Finally, a water injection test is performed to determine the presence of bleeding or leakage, after which a rubber drainage tube is placed in the pelvic cavity.

### Robotic natural orifice specimen extraction surgery via vagina

Following general anesthesia, the five-hole method is adopted in the lithotomy position with the right thigh placed horizontally. After cutting the first incision in the mesorectum 3–5 cm below the sacral headland, the Toldts gap is entered, after which the root of the inferior mesenteric vessels is freed. Being careful to protect the ureter while separating the bare inferior mesenteric vessels layer-by-layer with a pre-cut line, they are then ligated and cut, after which the mesorectum is freed. Afterward, the avascular area of the sigmoid mesocolon is opened. The assistant lifts the back of the mesorectum and frees it downward and outward 3–5 cm below the tumor. Then, the right rectal separation and the sigmoid colon and left rectal separation are performed. The mesorectum is transrectally cut about 5 cm below the tumor, baring about 2 cm of the intestine canal. The assistant instructs the surgeon to take a 3–4 cm incision in the posterior vaginal fornix by a bladder hook trans-vaginally. The stapler holder is then delivered into the abdominal cavity through the incision. The intestine canal is cut longitudinally 1 cm below the sigmoid rectal pre-cut line above the tumor, and the stapler holder is placed into the intestine through the incision, after which the sigmoid colon and naked area under the tumor are transected with a linear cutter stapler and cartridge. The assistant uses an oval forceps to deliver a sterile plastic protector into the abdominal cavity through the vagina. Together with the surgeon, the specimen is placed in the protector and then pulled out of the body using the oval forceps. An annular stapler is then placed through the anus, and the stapler holder is docked with the body in order to complete the end-to-end anastomosis. Finally, the water injection test was done to check for the presence of bleeding or leakage. After venting abdominal cavity gas, the incision was sutured in the posterior vaginal fornix with a barbed suture, and a rubber drainage tube was placed in the pelvic cavity.

Operation video, key part photos, surgical resection specimens, and other imaging materials should be kept during the operation.

### Postoperative management

Patients in both groups will receive the same care after surgery, and adjuvant therapy will be implemented in accordance to the NCCN guidelines for colon and rectal cancer.

### Primary outcomes

Incidence of surgical complications 30 days postoperative. The classification of surgical complications will be classified using the Clavien-Dindo system.

### Secondary outcomes

The following secondary outcomes will be measured: (1) Surgical stress response (i.e., the variation of C-reactive protein, interleukin-6, interleukin-10, cortisol, and lymphocyte subsets count of CD3, CD4, and CD8). All indicators will be tested the day before surgery as well as on the first, third, and fifth day after surgery; (2) the positive rate of malignant cells in the ascitic fluid specimen that will be used to assess the quality of the surgical quality; (3) the positive rate of bacterial culture in the ascitic fluid specimen that will be used to assess the quality of the surgical quality; and (4) general conditions such as postoperative pain score on the first day following surgery using the visual analog score, which will be tested the day after surgery, time to first flatus, time to leave bed postoperatively, time to first liquid diet postoperatively, postoperative hospital stay, operation time, estimated blood loss, and the number of retrieved lymph nodes. The timeline of the measurement of these indicators is shown in Fig. 2.

### Data collection and management

The corresponding investigator in each hospital will gather the medical information and guarantee its accuracy. Moreover, the medical information will be stored in the medical record system. Private information like participants’ names will be erased and replaced by an identification number. Each investigator logs into this system using a private account, and the overall data is only accessible by the principal investigator. An individual blinded to the allocation and surgical processes will conduct the final statistical analysis, and no interim analysis will be performed. As both groups are low-risk intervention, no auditing trial is needed. The sponsor, [name], initiated this trial and has the ultimate authority over this trial. The results of this trial will be shown in the publication.

### Statistical analysis

Non-inferiority analysis of primary outcomes will be performed in the per-protocol population using the chi-squared test with a one-sided significance level of 0.025, in which the power to detect the surgical complication rate difference is 0.8. The per-protocol population refers to cases that completed the corresponding treatment in each group. All analyses will be performed using SPSS 22.0 (IBM, USA). Both primary and secondary outcomes will be analyzed in accordance with the per-protocol principle. Subgroup analyses will be performed on these variables: gender (between male and female), approach (between vagina and rectum), and cT stage. Unadjusted *p* values will be reported but the number of declared subgroups analyses will be specified in all publications. Multiplicative interaction analysis will be applied, as appropriate.

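### As worded, the primary non-inferiority analysis is a chi-squared test of zero difference that never uses the 10% margin

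*Protocol article*

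**What the plan says.** The Statistical analysis section of the protocol article names the primary test: "Non-inferiority analysis of primary outcomes will be performed in the per-protocol population using the chi-squared test with a one-sided significance level of 0.025". It adds a statement about power: "in which the power to detect the surgical complication rate difference is 0.8". That section contains no margin, no confidence interval for the difference in rates, no shifted null hypothesis and no rule for declaring success.

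The margin appears in the Abstract and in the Sample size section: "After a close discussion with the investigators involved in this trial, the margin was set to 10" per cent. The Sample size section also gives 80% power, a one-sided level of 0.025, 402 evaluable patients (201 per group), 503 after allowing for 20% dropout, and a final figure of 550.

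**The concern.** The null hypothesis of the ordinary chi-squared test is RN = RA. The null hypothesis of this trial is that RN minus RA is at least 10 percentage points. The first can be rejected or retained without saying anything about the second.

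An analyst who follows the sentence literally obtains a p-value against equality and must then decide what it means for non-inferiority. Two readings are possible:

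- **Success requires a significant result in favour of RN.** The trial becomes a superiority trial, and the stated 80% power is lost.
- **Success is the absence of a significant difference.** The stated 0.025 error rate is lost, and a smaller or noisier trial finds it easier to succeed.

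This is the only primary analysis, and it decides the trial's conclusion on the safety of a new technique. The trial is open-label, and the article does not fix which reading applies before results are known.

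**Working it through.** **Inputs**

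- Control rate 15% (Sample size: "the complication rate of traditional robotic-assisted surgery is around 15" per cent); the published alternative is 17%.
- Margin 10%, taken as an absolute difference of 0.10.
- One-sided level 0.025, power 80% (Sample size).
- 1:1 allocation (Randomization and blinding).

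**1. Reproduce the plan's sample size.** For a margin-based test with equal true rates p:

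n per group = (1.960 + 0.842)² × 2p(1 − p) / margin²

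- p = 0.15: 7.849 × 2 × 0.15 × 0.85 / 0.10² = 200.1, rounded up to 201. The total is 402, and 402 / 0.8 = 502.5, rounded up to 503. All three match the plan.
- p = 0.17: 222 per group (444), so the plan used 15%.

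**2. Would a zero-difference test give the same number?**

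- 15% against 25%: 250 per group (270 with continuity correction).
- 15% against 5%: 141 per group.

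Neither gives 201. The trial was sized for a test against the margin.

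**3. Operating characteristics.** These come from exact enumeration of two independent binomials, with RA at 15%. The margin-based rule is that the upper limit of the two-sided 95% Wald interval for RN − RA does not exceed 0.10. The chi-squared test is the ordinary pooled test, without continuity correction, of zero difference at 0.05 two-sided (0.025 in each direction).

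| Evaluable per group | True RN rate | Margin-based rule succeeds | Chi-squared significant, favouring RN | Chi-squared not significant |
|---|---|---|---|---|
| 201 | 15% | 80.3% | 2.5% | 95.1% |
| 201 | 25% (at the margin) | 2.55% | 0.0% | 28.5% |
| 220 | 15% | 83.7% | 2.5% | 95.0% |
| 220 | 25% | 2.6% | 0.0% | 25.0% |
| 275 | 15% | 90.8% | 2.5% | 95.0% |
| 275 | 25% | 2.6% | 0.0% | 16.0% |

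Here 220 per group is 550 × 0.8 / 2, and 275 is 550 / 2. Relative to 2.5%, the false-claim rate under the *not significant means non-inferior* reading is 28.5 / 2.5 = 11.4 times at 201, 10 times at 220 and 6.4 times at 275.

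The margin-based result depends little on the interval chosen. The Farrington-Manning test gives 79.4% power at 201 per group and 83.1% at 220, with a type I error of 2.5% at the margin.

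**4. Illustrations at 201 per group**

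| RA events | RN events | RN − RA | Chi-squared | Two-sided p | 95% CI | Non-inferior at 10 points? |
|---|---|---|---|---|---|---|
| 30 | 30 | 0.0% | 0 | 1.00 | −7.0% to +7.0% | Yes |
| 30 | 36 | 3.0% | 0.65 | 0.42 | −4.2% to +10.2% | No |
| 30 | 43 | 6.5% | 2.83 | 0.093 | −1.0% to +14.0% | No |

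All three are non-significant on the chi-squared test, yet only the first shows non-inferiority.

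**The case against.** The strongest defence is that the sentence should be read with the rest of the design. It calls the analysis a non-inferiority analysis and gives it a one-sided level, whereas an ordinary 2×2 chi-squared test has no direction. The margin, level and sample size are all fixed elsewhere, and margin-shifted score tests of chi-squared type exist. On that view the intended hypothesis can be recovered, and the exact null, interval and decision rule belong in the full protocol or SAP, which are not shown.

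Part of this stands:

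- The margin is prespecified. What is missing is its use in the named test.
- The wording about power to detect a difference is weak evidence of a difference test, because the Sample size section uses similar wording ("We assume that this trial has 80% power (1-β) to detect the complication rate difference between the experimental and control group") beside a correct non-inferiority calculation.
- A significant one-sided result favouring RN would logically imply non-inferiority, so it would be too strong to say that the test can never show it.
- The 2.5% and 16.0% to 28.5% figures each depend on a success rule that the article does not state.

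The central point is unaffected. The article does not leave the method open: it names one for the primary hypothesis, and that method, as ordinarily understood, tests the wrong null. Nothing in the text indicates a shifted statistic, and someone running the named test in SPSS 22.0, the stated software, would reasonably run the ordinary one. If a margin-shifted test was meant, the sentence still needs correcting.

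**Conclusion.** The concern holds and must be fixed before analysis. The named primary test does not address the hypothesis for which the trial was sized, and neither way of using its p-value gives both the stated 80% power and the stated 0.025 error rate. With 201 evaluable per group, requiring significance in favour of RN gives a 2.5% chance of success at equal rates, against 80.3% for a margin-based limit. Treating non-significance as success gives a 28.5% false-claim rate at the margin (25.0% at 220 per group, 16.0% at 275), against about 2.5%.

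These figures assume an RA rate of 15%, an absolute 10-point margin (the reading that reproduces the plan's 201) and an ordinary chi-squared test of zero difference. The sample size itself is correct and is not in dispute.

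**What to change.** Replace the test named in the Statistical analysis section with an explicit hypothesis and decision rule, for example:

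> The null hypothesis is that the 30-day complication rate in RN exceeds that in RA by 10 percentage points or more. RN is declared non-inferior if the upper limit of the two-sided 95% confidence interval (Miettinen-Nurminen) for the risk difference RN − RA is below +10 percentage points.

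A Farrington-Manning test against the margin at one-sided 0.025 would serve equally well, as would another valid margin-based limit, provided one is named in advance. Keep the chi-squared test for comparisons where a zero-difference null is intended, such as superiority. If SPSS 22.0 does not provide the chosen interval, allow other software for this analysis.

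The cost is a sentence or two of analysis wording. Sample size, recruitment and data collection do not change.
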